## Abstract

**Background:**

Physical inactivity is pervasive and prevalent in the United States, particularly among women of low socioeconomic position and women with children. Structural and social barriers make active leisure time a rare commodity, creating a pressing health issue because physical inactivity increases the risk of chronic diseases and poor health.

**Objective:**

The broad objective of this study is to test the effectiveness of Free Time for Wellness, a multilevel intervention to increase physical activity among low-resourced mothers.

**Methods:**

This study comprises a 3-arm parallel cluster randomized controlled trial (RCT) with low-resourced mothers living in New York City. We will randomize fitness class sites (clusters) into arm A (contact control), receipt of free weekly fitness classes; arm B, receipt of free childcare combined with free weekly fitness classes; and arm C, receipt of free childcare combined with free weekly fitness classes and peer support activities. Over 2 years, we will recruit a pilot wave followed by 7 additional waves, totaling 720 participants into 24 fitness classes. Physical activity is the primary outcome, measured using accelerometers, but secondary outcomes also include physical activity assessed using a self-reported questionnaire and attendance data. We will assess additional secondary outcomes (eg, health status, depression, and anxiety) and mediators or moderators (eg, social support and cohesion) with a baseline and follow-up questionnaire. The intention-to-treat analysis will use linear mixed-effects models to assess the main intervention effects on physical activity outcomes and other secondary outcomes. Ethnographic methods will examine how intersecting forms of social identity shape women’s experiences of physical activity and understand how real-world conditions shape the intervention implementation.

**Results:**

The study received funding from the US National Institute of Health, covering the period of time from April 1, 2023, through March 31, 2028. We received initial institutional review board approval in August 2023. The study is active and recruiting participants. As of the day of manuscript submission, we have enrolled 471 participants. Data collection is anticipated to occur until September 2026 for primary completion. The estimated study completion date is December 2026. Dissemination of the results will take place with participants, community members, partners, and researchers through methods such as reports, websites, events, and academic publications and conferences.

**Conclusions:**

This cluster RCT tests whether access to childcare (an understudied structural barrier) and social support can increase physical activity. The study design and outcomes integrate ethnographic methods with a cluster RCT to better understand mechanisms and the impact of intersecting factors such as race or ethnicity, culture, gender, and socioeconomic position. The study leverages widely accessible, existing resources to promote physical activity and foster social support with the ultimate goal of assessing the effect of childcare access on parental health.

**Trial Registration:**

ClinicalTrials.gov NCT06654843; https://clinicaltrials.gov/study/NCT06654843

**International Registered Report Identifier (IRRID):**

DERR1-10.2196/71381

## Introduction

More than 46% of US men and women do not achieve the recommended physical activity guidelines for aerobic activity each week, and 76% do not meet the guidelines for both aerobic and muscle-strengthening activity [1]. This is important because physical inactivity contributes to an increased risk of chronic diseases and poor health. Physical inactivity is particularly prevalent in women of low socioeconomic position (SEP; 60% are inactive), suggesting that there are structural barriers to being physically active. Proposed mechanisms through which low SEP may influence physical inactivity include increased biological stress, increased risk of poor health due to reduced access to health care, and reduced access to other resources such as physical activity facilities and gymnasium memberships [2].

Our previous research identified that an additional barrier for women who are mothers is having the free time to be physically active [3]. This is also supported by other research showing that women with children tend to be less physically active than women of the same age without children, due to structural and social barriers that reduce active leisure time [4,5]. For resource-limited mothers in particular, social and environmental barriers to physical activity include family expectations, lack of transportation, insufficient financial resources, unsafe environments, and a lack of childcare [4]. Childcare and household duties cause significant stress and exhaustion for mothers, with mothers describing parenting as “relentless” (yet also acknowledging its rewards) [6]. There is a large existing body of literature examining wellness interventions for mothers. However, most studies focus only on promoting physical activity during pregnancy or the postpartum period (and not later in motherhood), when being physically active without childcare is easier because young babies can be included in the mother’s activities, such as going for stroller walks. This focus is illustrated by the large number of systematic reviews focused on interventions in these periods [6]. In addition, while a lack of childcare is a well-known barrier to mothers’ physical activity, backed by research, very few studies explicitly address this barrier as part of an intervention [4,7] For example, in a systematic review of group-based physical activity interventions for postpartum women, none of the studies provided childcare, although many studies have identified it as a barrier to being physically active [8].

This study will add to a small but important body of literature on how mothers’ health can be improved by addressing the unique challenges that mothers face in finding time and space for their health and well-being. Some limited evidence suggests that physical activity opportunities for mothers, when children are being cared for by others, can lead to reduced stress and improved BMI, lower resting heart rate, and normal blood pressure in comparison to controls [7,9]. An older systematic review of physical activity and parenthood found that “social support and childcare were paramount in alleviating physical activity barriers, especially for mothers” [8].

To address the need for mothers to find time and space for physical activity, we will test a first-of-its-kind intervention that we co-designed [3] and piloted with mothers [10], which provides free childcare in combination with a novel peer support system. Based on prior theory and our pilot work [11,12], we hypothesize that free childcare and peer support will increase physical activity, and no previous health interventions have studied this. Expanding research on social cohesion suggests that individual adoption of health behavior is much more likely when participants receive social reinforcement from multiple neighbors in their social network [13,14]. For example, a systematic review of randomized controlled trials (RCTs) of group-based physical activity for mothers of young children found evidence of increases to self-reported physical activity and psychological well-being [15]. Further, while resource-limited mothers reported that peer support encourages their participation in physical activity [5], another study found that higher-income mothers were significantly more likely to report friends or family offering to be physically active with them [6]. Our co-designed intervention, the Free Time for Wellness (FT4W) program, will generate novel access to individual- and community-level resources and will leverage peer support among mothers in urban, racially segregated, low-income communities in New York City.

The broad objective of this study is to test the effectiveness of FT4W, an innovative multilevel physical activity intervention to increase physical activity and ultimately reduce the risk of chronic diseases and improve mothers’ well-being. We will do so via the following specific aims:

Aim 1: conduct a parallel cluster RCT to evaluate the effectiveness of providing free childcare at free fitness classes to increase physical activity among low-resourced, historically minoritized mothers.Aim 2: test if peer support enhances the effect of the childcare intervention on physical activity by including another intervention arm promoting social cohesion.Aim 3: integrate ethnographic methods throughout the RCT to understand how individual-, community-, and institutional-level factors modify and influence the effect of the intervention, with particular attention to intersectional inequalities.

The saying “it takes a village” captures an existing cultural phenomenon of mothers supporting mothers through in-person and virtual “mom groups” [12]. FT4W builds from this concept, combining cultural context, the science of social cohesion, co-design methodology, and mixed methods to bolster mothers’ support networks and help promote their wellness. If effective, the FT4W program will illustrate how supporting mothers at the community level can increase physical activity, thus reducing chronic disease disparities in communities with high social inequality by providing resources, building social cohesion, and freeing up time for mothers to focus on their own wellness.

## Methods

### Study Design

This study comprises a 3-arm parallel cluster RCT with low-resourced mothers living in New York City. The trial has been planned, and this protocol is reported in line with the CONSORT (Consolidated Standards of Reporting Trials) statement [16].

The complete FT4W program includes free childcare at weekly fitness classes and peer support activities. We will randomize fitness class sites (clusters) into arm A, a contact control, receiving only the free weekly fitness classes; arm B, receiving free childcare provided at the same location as free weekly fitness classes; or arm C, receiving free childcare at free weekly fitness classes, plus peer support activities.

### Theoretical Framework and Logic Model

The FT4W program is founded on social cognitive theory, which posits that human behavior is the product of the dynamic interplay of personal, behavioral, and environmental influences [17]. Social cognitive theory emphasizes reciprocal determinism in interactions between people and their environments. The majority of physical activity interventions use social cognitive theory as indicated by the theory and technique tool developed by the Human Behaviour Change Project [18]. We used the theory and technique tool to align the FT4W program components and mediating pathways with behavior change techniques and mechanisms of action substantiated in behavior change literature and expert consensus. Studies that use behavior change techniques of restructuring the physical environment and peer support show that the mechanisms of action are environmental context and resources (aspects of a person’s situation or environment that discourage or encourage the behavior) and social influences (interpersonal processes that can cause oneself to change one’s thoughts, feelings, or behaviors) [18]. For our study, we will measure social influence via social cohesion.

Our logic model (Figure 1) illustrates the 2 complementary components of the FT4W program and mediating pathways in which the intervention can be effective. We hypothesize that providing free childcare during free fitness classes can provide environmental resources that participants can use to increase their physical activity. We hypothesize that this effect will be stronger in participants who also receive peer support, the intervention component that creates social cohesion. We also hypothesize that the effect of the intervention will differ based on race and ethnicity and other social stratifiers (migration status, SEP, and gender or sexual orientation).

**Figure 1 figure1:**
[figure not shown]
Logic model for Free Time for Wellness program.

### Patient and Public Involvement

The intervention was developed in this New York City–based study through a co-design process with women from Washington Heights, New York City [3,10]. We established collaborations with 3 community partner organizations (Shape Up NYC, Jovie, and the West Side Campaign Against Hunger [WSCAH]). These partners participate in research team meetings and in the study design. Partner details are provided as follows:

Shape Up NYC: New York City Department of Parks and Recreation programs include Shape Up NYC, a free group fitness program offering 87 fitness classes at 60 locations across the 5 New York City boroughs. Shape Up NYC will determine and schedule available study sites and classes in coordination with the intervention.Jovie: Jovie is a professional childcare company that provides care for families and businesses. We partnered with Jovie during the feasibility study, and they will continue providing childcare.WSCAH: WSCAH is one of the largest food pantries that serves New York City and is distinctly committed to providing healthy food through a customer-choice supermarket-style pantry. WSCAH will coordinate volunteer activities and food delivery for participants in the arm receiving peer support.

These partners are members of our community advisory board (CAB). The CAB also includes 4 community liaisons and 2 community champions. The community liaisons are individuals who represent or serve our target communities, the community partners represent our organizational partners, and the community champions are local women who will help facilitate peer support activities.

The main CAB functions are to ensure that the study’s research strategies and design respect and serve our participants and make sense “in the real world.” The CAB will meet quarterly to troubleshoot any problems with the trial procedures. They will also bring community concerns or ideas to the research team.

### Participants

#### Eligibility Criteria

The trial will enroll mothers aged 18 years and older, who understand or speak English or Spanish, have children younger than 12 years of age (because younger children require more care, and we are focused on preventing chronic disease among premenopausal women), own a mobile phone, and live in nearby zip codes surrounding Shape Up NYC sites. Mothers must also meet income requirements, with total household income less than or equal to 165% of the area median income (calculated by household size).

#### Clusters

We will recruit 720 participants into 24 Shape Up NYC classes, across 1 pilot wave (n=90) and 7 study waves (n=630) over 2 years (Figure 2). Shape Up NYC class sites that allow research and have adjacent space for childcare will be eligible for selection. We will randomize each wave of 3 sites into 1 of 3 arms, using computer-generated random numbers, and run the program for 12 weeks. We will first randomize the class sites and then recruit participants into them while blinded.

**Figure 2 figure2:**
[figure not shown]
Staggered recruitment.

For each wave, 30 participants will be recruited into each class (n=90 per wave). This process will be repeated for each wave with 3 classes, some of which will be located at the same sites as previous classes in previous waves. We will stratify randomization by geographic location and across seasons. While we cannot stratify on individual-level factors in a cluster RCT, stratification by geographic location will help to capture many social demographic factors at the individual level (eg, race or ethnicity and income level). In addition, Shape UP NYC trains fitness instructors at all sites following the same curriculum, and all arm C participants will have the same community champions (described more in the Peer Support Activities (Arm C Only) section).

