#### Sample Size

We powered the study to compare the main intervention effects on the primary outcome, which is the average time spent in moderate to vigorous physical activity (MVPA) per week. We plan to enroll 7 sites per study arm (excluding the pilot wave), with about 30 participants with up to 45 children per site. We assume an attrition rate of 30% based on our feasibility study as well as another similar study [19] and an additional 25% accelerometer nonadherence rate based on previous studies [19,20], yielding an average 15 participants per site. Previous studies show that the intraclass correlation coefficient is ~0.15, and we expect a coefficient of variation of 0.5 in the number of participants across different sites. For aim 1, with 80% power, the minimum detectable effect size for the comparison of intervention arm B versus control arm A on average time spent in MVPA is Cohen *d*=0.68 at 5% significance. For aim 2, we will use the Bonferroni correction to adjust for multiple comparisons of arm C versus arm B and arm C versus arm A. With 80% power, the minimum detectable effect size for each comparison is Cohen *d*=0.75 at 5% significance. A previous physical activity intervention study with mothers led to an 80-minute increase in average time spent in MVPA [20]. Specifically, at posttest, the experimental group performed a mean of 154.8 (SD 45.3) minutes of physical activity, whereas the control group reported a mean of 74.6 (SD 44.4) minutes. This yields an effect size of *d*=1.8; thus, we are adequately powered for aims 1 and 2. Finally, quantitative analyses are not fully appropriate to examine intersectionality (eg, too reductionist), rendering a power analysis inappropriate; instead, we will integrate the statistical analysis with qualitative data to evaluate aim 3.

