#### Analyses

##### Quantitative Analysis

The primary analyses will be on the intention-to-treat sample: all randomized participants according to the assigned treatment. Missing data on outcome variables will be dealt with by using multiple imputation or inverse probability weighting of cases with complete data, where we will calculate weights based on the probability of a participant being a completer versus a dropout. We will conduct a sensitivity analysis to provide a range of plausible effect estimates that could arise due to nonignorable missing data.

For aims 1 and 2, we will use linear mixed-effects models (LMMs) to assess the main intervention effects on physical activity outcomes and other secondary outcomes. The outcome measure of interest will be the dependent variable; the treatment arm (categorical variable with 3 categories) will be the predictor. Cluster-specific random intercept will account for intraclass correlation. We will further adjust the model for baseline covariates that are not balanced across treatment groups (if any). Comparison of treatment arms can be tested by forming contrasts of regression coefficients in the models.

We will conduct mediation analysis to test whether environmental resources and social cohesion, described under working mechanisms, mediate the intervention effects. For each mediation analysis, we will conduct 2 LMM analyses. The first model will use the outcome measure as a dependent variable and treatment arm and mediator as predictors. The second model will use the mediator as a dependent variable and treatment arm as the predictor. Both models will include a cluster-specific random intercept to account for intraclass correlation. Causal mediation effects will be tested using the R package *mediation*. For aim 3, moderator analysis will examine whether intervention effects differ across social stratification parameters (stratifier) at the individual and community levels. We will conduct a similar LMM analysis as in the main effect analysis, with the exception that each stratifier and its interaction with the treatment arm will be included in the LMM. The moderator effect will be examined by testing the stratifier by treatment interaction effect coefficients.

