While 21 clusters are on par with the average cluster size in cluster RCTs, we still need to correct for the small sample since type I error can be up to ~7% for studies with 20-40 clusters [45]. For our continuous outcomes, residual (restricted) maximum likelihood will be used [46]. We will also adjust the test statistic to a 2-tailed *t* test with 2K–2 degrees of freedom if cluster structures are balanced [47]. If cluster sizes vary, alternative small sample corrections will be used. As a sensitivity analysis, cluster-level analysis will also be conducted. We will perform a 2-tailed *t* test on the cluster-level means of physical activity.

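### The trial randomises sites in waves of three, one per arm, but the written analyses omit wave; if activity varies between waves, intervals are wider than needed and tests conservative

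*Protocol article*

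**What the plan says.** **Randomisation.** The Clusters section of the protocol article says "We will randomize each wave of 3 sites into 1 of 3 arms, using computer-generated random numbers". The text after Figure 2 adds "We will stratify randomization by geographic location and across seasons" and notes that later waves include classes "some of which will be located at the same sites as previous classes in previous waves". The Sample Size section says "We plan to enroll 7 sites per study arm (excluding the pilot wave"). Seven study waves of three sites, with seven sites per arm, are naturally read as one site per arm in each wave.

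**Analysis.** The Quantitative Analysis section specifies a linear mixed model with the three-level treatment arm as predictor and states "Cluster-specific random intercept will account for intraclass correlation". Further adjustment is limited to baseline covariates found to be imbalanced between arms. The cluster-level sensitivity analysis is a two-tailed t "test on the cluster-level means of physical activity". Wave, season and location appear in neither analysis.

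**The concern.** Each wave contributes one site to each arm, so whatever is common to a wave (season, weather, calendar time) cancels from every comparison between arms. An analysis without wave does not know this. It counts wave-to-wave differences as between-cluster noise and puts them back into the standard error. The point estimate is still unbiased, but the interval is wider than the design warrants and the test rejects too rarely under the null.

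The covariate rule is unlikely to repair this. It is triggered by imbalance, and blocking makes wave, and season within it, balanced across arms.

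This is not a detail left to an unseen analysis plan. The protocol writes out the fixed effect, the random effect, the covariate rule, the estimation method and a degrees-of-freedom rule, and the analysis so described does not match the randomisation. What is at stake is precision in a trial with 21 clusters.

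**Working it through.** **Inputs from the Sample Size section.** K = 7 clusters per arm; ICC = 0.15; m = 15 ("yielding an average 15 participants per site"); 80% power; 5% level for aim 1; Bonferroni over two comparisons, so 2.5% each, for aim 2.

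**Assumption.** The share of the ICC that lies between waves is not in the document. It is varied from 0 to 75%.

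**Step 1: the plan's own figures.** Design effect = 1 + (15 − 1) × 0.15 = 3.10. Minimum detectable effect = (z for alpha + z for power) × √(2 × 3.10 / (7 × 15)).
- Aim 1: (1.960 + 0.842) × 0.243 = 0.681, stated as 0.68.
- Aim 2: (2.241 + 0.842) × 0.243 = 0.749, stated as 0.75.

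Both reproduce as an unblocked comparison with a normal approximation and equal cluster sizes. Wave plays no part.

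**Step 2: variance of a cluster mean.** In units of the total SD squared: 0.15 + 0.85/15 = 0.2067. If a share s of the ICC is common to the wave, the variance that enters an arm contrast is 0.2067 − 0.15s. The planned analyses still estimate about 0.2067. The standard error is therefore too large by the factor √(0.2067 / (0.2067 − 0.15s)). For s = 50% this is √(0.2067/0.1317) = 1.25.

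**Step 3: degrees of freedom.** A two-way (wave, arm) analysis of 21 cluster means leaves (7 − 1) × (3 − 1) = 12 df. The plan's rule gives 2K − 2 = 12. An unblocked analysis pooling all three arms has 21 − 3 = 18.

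**Step 4: simulation.** Cluster means were simulated for 7 waves × 3 arms, treated as 21 independent clusters apart from the shared wave effect. The planned analysis is the two-sample t test on 12 df. The alternative is the two-way analysis on 12 df. Results are for B versus A:

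| Wave share of ICC | SE too large by factor | True type I error, planned | 95% half-width (SD): planned / with wave | Power at d = 0.68, 5% level: planned / with wave |
|---|---|---|---|---|
| 0% | 1.00 | 5% | 0.52 / 0.52 | 73% / 73% |
| 10% | 1.04 | 4.3% | 0.52 / 0.50 | 74% / 76% |
| 25% | 1.11 | 3.3% | 0.52 / 0.47 | 75% / 81% |
| 50% | 1.25 | about 2% | 0.52 / 0.41 | 77% / 90% |
| 75% | 1.48 | 0.9% | 0.52 / 0.35 | 79% / 97% |

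With wave in the analysis the type I error is about 5% throughout. For aim 2, at d = 0.75, the 2.5% level and a 50% share, power is 73% as planned against 89% with wave.

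**Step 5: the stricter comparison.** The unblocked three-arm analysis on 18 df has a mean half-width of about 0.50 SD at every share. Against it, the wave-adjusted interval is about 3% wider at a 0% share (0.519/0.504) and about 1% narrower at 10% (0.499/0.503). It is about 7% narrower at 25% (0.469/0.503), 18% at 50% (0.414/0.502) and 30% at 75% (0.350/0.500).

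**The case against.** **The loss is conditional.** If wave carries no outcome variance, nothing is lost, and at a 10% share the loss is small. This stands, and it is why the range starts at zero. The protocol does, however, treat season as worth stratifying on.

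**No false-positive risk, and ample stated power.** The Sample Size section plans on d = 1.8 against detectable effects of 0.68 and 0.75, so on the plan's own assumption no conclusion would change. This limits the severity. It is not a reason to leave the blocks out, since the interval is reported whatever the effect turns out to be.

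**Net direction.** The calculation takes the 21 clusters as independent apart from wave. Sites reused in later waves create a separate dependence that could push the error the other way. This stands: the figures isolate the effect of omitting wave and do not describe the total error.

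**Location.** The article does not say how location is stratified within a wave of three sites, or how many levels it has. Four location terms, for example, would reduce 12 df to 8 and raise the critical t from 2.18 to 2.31. The case made here is for wave.

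**The degrees-of-freedom rule.** A reader might infer that 2K − 2 is also wrong, as a two-arm formula for balanced clusters in a three-arm trial that expects a coefficient of variation of 0.5. The document does not support this as a fault. Pairwise contrasts are two-arm comparisons, and the same section provides for other small-sample corrections when cluster sizes vary. Which correction to use is a matter of preference.

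**Conclusion.** The mismatch holds: the protocol randomises in blocks of one site per arm per wave, and neither written analysis includes the block. A reader might go further and infer that the planned intervals are definitely too wide. The document does not support that, because it gives no between-wave variance. What can be said is that the planned analyses are conservative to the extent that activity varies between waves or seasons. Over assumed wave shares of 10 to 75% of the ICC, the standard error is too large by 4 to 48% and the true type I error of the nominal 5% t test falls to between 4.3 and 0.9%. With no wave variance there is no loss.

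These figures rest on ICC 0.15, 15 participants in every cluster and 21 clusters that are independent apart from wave. The change is worth making because its possible gain is substantial and its cost is close to nil. It does not threaten the trial's validity.

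**What to change.** - Prespecify wave, as the randomisation block, as a fixed effect in the primary and secondary mixed models, regardless of any observed imbalance.
- Run the cluster-level sensitivity analysis as a two-way (wave, arm) analysis of cluster means on 12 df in place of the plain t test.
- Add location only if it is an actual randomisation stratum, is not nested in wave and has few levels, since each term costs degrees of freedom. Season needs no separate term if each wave falls in one season.
- State separately how classes at a reused site are handled. A wave term does not address that dependence.

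**Cost.** Analysis wording only, with no change to data collection or enrolment. If wave explains nothing, the interval is unchanged against the 12-df rule and about 3% wider than that of an unblocked three-arm analysis on 18 df.
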